**Primary outcomes**									
	RSE^a^	Items modelled on Self-efficacy to Deal with Violence Scale [48,49]		RSE-self (2) RSE-others (2)		0=not at all confident 3=very confident		0-6 0-6	
**Secondary outcomes**									
	WB^b^	World Health Organization-Five Well-Being Index [50] used in children [51,52] and in New Zealand youth [53,54]. Modified “I have felt active and vigorous” to “I have felt active and full of energy”		WB (5)		0=at no time to 5=all the time		0-25	
	General health	Single 5-point Likert scale to rate respondent’s general health		General health (1)		0=poor to 4=excellent		0-4	
	Connectedness	Retained 2 subscales from Hemingway Measure of Adolescent Connectedness [55] with language regionalized and negatively worded items not scored		Connectedness-family or whānau (5) Connectedness-friends (5)		0=not at all true 4=very true		0-20 0-20	
	Cybersafety	15-item questionnaire began with a scenario modified from the Coping with Cyberbullying Questionnaire [56]; items are from original research with young Māori women [57]		Cybersafety–being safe (7) Cybersafety–taking action (8)		0=definitely not 3=definitely yes		0-21 0-24	

^a^RSE: relationship self-efficacy.

^b^WB: well-being.

The Cyber-Safety questionnaire was developed from original research on young Māori women [57]. The 15-item questionnaire begins with a scenario modified from the Coping with Cyberbullying Questionnaire [56], as follows:

Imagine that for a few weeks, you have been receiving nasty and threatening text messages. Aside from that, you found out that embarrassing pictures of you are being spread around.

Taitamariki then respond how likely they would be to use each of the 15 strategies to keep yourself safe on the internet (eg, I would talk to my friends about it, I pay attention to who has access to my data). Other secondary outcomes include well-being, general health, and connectedness (Table 3).

The baseline data (preimplementation of the intervention acquired in all schools before the transition period) will be extensively analyzed, leading to a full analytical design. In particular, exploratory factor analysis of the outcomes will lead to the creation or confirmation of subscores, making RSE, connectedness, and cybersafety bivariate outcomes.

#### Randomization

Schools are stratified by size (small or large). Large schools are further stratified by ongoing standardized delivery of a healthy relationship program (HRP). Within each stratum, the school labels are randomly ordered using a computer-generated sequence of pseudovariates. They are then assigned in this random order to the first sequence period (year 1, term 2: 2 small schools, 1 large school with HRP, and 1 large school with no HRP), and then the second sequence period (year 1, term 3: 1 small school, 2 large schools with HRP, and 1 large school with no HRP).

#### Analysis

The data will be kept stratified within the clusters by gender, Māori versus non-Māori ethnicity (hereafter identified as ethnicity), and year-group. The year-group (years 9-13) is defined as usual for the first 4 periods and crosses over to the next nominal year-group in the fifth period, so that each year-group defines a subcohort followed over time. The year 9 group from period 5 is identified as a separate year-group. The analysis sets consist of intention-to-treat, as-treated, and adopter (students reporting app use) sets. All primary analyses will take place in the intention-to-treat set. General effectiveness hypotheses will be tested using a linear mixed model with nested participant, year-group, and school random effects. All models will initially be fitted with the function *lme* from the R package *nlme* [58]. If the results fail to converge or otherwise display poor numerical behavior, PROC MIXED from SAS/STAT version 9.4 (SAS Institute Inc) will be used instead. 

To ensure the overlap of the intervention and control in the design, data will be collected during the transition periods and included in the analysis, assuming an intervention effect half the size of that in the posttransition periods. This approach is nonstandard but necessary in this instance and broadly plausible under the conditions of implementation and the nature of the intervention.

Māori subgroup analyses are planned. They will consist of all primary analyses limited to Māori participants. Subgroup analyses will take place in the intention-to-treat and as-treated sets. It will extend to all outcomes covered by primary analyses.

A blind review of the data will take place (before allocation unblinding) to determine whether any transformation is necessary, to settle on the final models, and to determine whether any missing covariate or outcome data require multiple imputation, and generally to finalize the statistical analysis plan. All tests will be performed at a 5% significance level against 2-sided alternatives. There are no circumstances in which unblinding is permissible.

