### Trial Design

A pragmatic, stepped wedge, cluster randomized (one-directional crossover) trial in 8 pilot secondary schools tests the effectiveness of the Harmonised app. Secondary schools in New Zealand include years 9 through 13 (5 years of high school, generally young people aged 13 to 17 years). In the stepped wedge design, the app is implemented in all 8 schools in one of 2 school terms, with the order of implementation determined at random [41-44]. There are 5 assessments (web-based surveys) per school and 2 time steps over a 15-month trial period (Table 2). Our protocol description follows the CONSORT (Consolidated Standards of Reporting Trials) stepped wedge, cluster randomized trial extension [44]. The study was registered with the Australian New Zealand Clinical Trials Registry (ACTRN12619001262190) on September 12, 2019.

**Table 2 table2:** Stepped wedge implementation design plan.

School ID Number	Year and school term					
	Year 1					Year 2, T1^a^
	T1^a^	T2^a^	T3^a^	T4^a^		
8	CC^b^	CC	TP^c^	IC^d^	IC	
7	CC	CC	TP	IC	IC	
6	CC	CC	TP	IC	IC	
5	CC	CC	TP	IC	IC	
4	CC	TP	IC	IC	IC	
3	CC	TP	IC	IC	IC	
2	CC	TP	IC	IC	IC	
1	CC	TP	IC	IC	IC	

^a^T1 to T4 are the terms for the implementation of the design plan.

^b^CC: control condition.

^c^TP: transition period.

^d^IC: intervention condition.

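### The stated primary model has only time-constant random effects, so if school means vary from term to term, its standard error is too small and its 5% test anticonservative

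*Protocol article*

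**What the plan says.** The design is a cluster crossover in one direction: "A pragmatic, stepped wedge, cluster randomized (one-directional crossover) trial in 8 pilot secondary schools tests the effectiveness of the Harmonised app" (Trial Design). On timing: "There are 5 assessments (web-based surveys) per school and 2 time steps over a 15-month trial period". Four schools start in term 2 ("year 1, term 2: 2 small schools, 1 large school with HRP, and 1 large school with no HRP", Randomization) and the other four in term 3.

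The Analysis section fixes the model: "General effectiveness hypotheses will be tested using a linear mixed model with nested participant, year-group, and school random effects". It defines year-groups as subcohorts followed through the terms, so the year-group effect, like the school and participant effects, does not change over time. The transition term is analysed as half a treatment effect. On software: "All models will initially be fitted with the function" lme of the R package nlme, and then "If the results fail to converge or otherwise display poor numerical behavior, PROC MIXED from SAS/STAT version 9.4" as the fallback. On the test: "All tests will be performed at a 5% significance level against 2-sided alternatives". No degrees-of-freedom method is named. A blind review is to settle the final models and complete the analysis plan.

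The Sample Size section uses the Hussey and Hughes method with a school random effect, a fixed term effect and a single ICC of 0.07. It makes no distinction between within-term and between-term correlation.

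**The concern.** With these random effects, a school's mean may depart from the common term trend only through student-level noise. Anything specific to one school in one term (a local event, a competing programme, a change in who answers the survey) falls at exactly the level where treatment varies. It moves the treatment estimate and is absent from its standard error.

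The article itself suggests sources of such variation. Implementation plans are tailored by school, with sessions led by the school or by researchers. Some schools run other relationship programmes. The baseline survey is done in class with researchers present, while the four later surveys are answered independently after reminders, so the mix of responders can differ by school and term.

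At stake are the p-values and intervals for the primary outcome, the secondary outcomes and the Māori subgroup, since the primary analyses and their Māori repeats share this model.

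**Working it through.** **Inputs from the article.** 8 schools, 5 terms, 600 students (75 per school), 35% attrition at each later term (75 x 0.65 = 48.75), ICC 0.07. Treatment coding is (0, 0.5, 1, 1, 1) for four schools and (0, 0, 0.5, 1, 1) for the other four.

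**Assumed, because the article does not give them.** The between-term correlation of school effects (CAC), from 1.0 to 0.80. The within-student correlation r (the share of individual variance that is constant over time), from 0.3 to 0.7. Total variance is 1 and the school-by-term variance is 0.07 x (1 - CAC).

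**1. The plan's power figure.** The Hussey-Hughes standard error is 0.1706. Taking 0.25 as the full effect, 0.25/0.1706 - 1.96 = -0.49, which is 31% power and not 83%. Taking 0.50 as the full effect (so that 0.25 is the halved transition-term effect), 0.50/0.1706 - 1.96 = 0.97, which is 83.4%. With 0.60 the result is 94.0%. The stated 83% and 94% are reproduced only on that second reading, which is used below for power. Which reading is meant is a separate question.

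**2. Why term-specific shocks matter here.** The coding differs between the two sequences by (0, 0.5, 0.5, 0, 0). The estimate is therefore roughly twice the difference between sequences in terms 2-3, less that in terms 1, 4 and 5. A school-by-term variance v adds about 4 x (1/2 + 1/3) x (1/4 + 1/4) x v = 1.67v to its variance. At CAC 0.95, v = 0.0035 and the addition is 0.0058. Against a model variance of 0.124² = 0.0154 (r = 0.5, item 4), the true standard error is √0.0212 = 0.146, or 1.17 times the model's.

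**3. Full calculation.** GLS weights from the stated structure are applied to a true covariance with CAC below 1 (sandwich variance), and type I error = 2Φ(-1.96/ratio), where ratio = true SE/model SE. At r = 0.5 the ratio is 1.17, 1.31 and 1.56 for CAC 0.95, 0.90 and 0.80.

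| CAC | r = 0.3 | r = 0.5 | r = 0.7 |
|---|---|---|---|
| 1.00 | 5.0% | 5.0% | 5.0% |
| 0.99 | about 6% | 5.8% | about 6% |
| 0.95 | 8.1% | 9.3% | 12.0% |
| 0.90 | 11.3% | 13.5% | 18.4% |
| 0.80 | 17.2% | 21.0% | 28.4% |

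**4. Simulation with lme itself.** Null data, random effects school/year-group/participant, r = 0.5, year-group variance 0.02, 400 runs per row (Monte Carlo error about 1 point at the 5% level, about 2 at the 20% level).

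| CAC | mean model SE | true SD of estimate | type I error |
|---|---|---|---|
| 1.00 | 0.124 | 0.124 | 4.3% |
| 0.95 | 0.125 | 0.143 | 9.0% |
| 0.90 | 0.125 | 0.159 | 13.8% |
| 0.80 | 0.126 | 0.189 | 20.3% |

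The model's standard error barely moves while the true spread grows by half. By default lme tested treatment on about 1,558 df. At school-by-term level there are 40 - 8 - 4 - 1 = 27.

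**5. Does an error term at the right level help?** An analysis of school-by-term means with 27 df gave 5.3-5.6% in 20,000 runs. In the small 400-run sets, which share seeds, it ranged from 5.3% to 8.3%. A REML fit to cell means with a school-by-term variance gave 4.0-6.4% over CAC 1 to 0.90 (800 runs), even with a normal critical value.

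**6. Permutation.** The strata are 3 small schools (2 go first), 3 large with a programme (1 first) and 2 large without (1 first). That is 3 x 3 x 2 = 18 allocations, and 1/18 = 0.056 exceeds 0.05.

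**The case against.** The strongest reply is that the inflation is conditional. At CAC 1 the test holds its level (5.0% by formula, 4.3% in lme), and at 0.99 the error is only 5.8% (r = 0.5). The article gives no value for CAC. Term fixed effects absorb shocks common to all schools, and the reminders for surveys 2 to 5 all go out in week 5 of term, which removes some differences in timing. This stands: a reader might infer that the planned test certainly misses 5%, and the article does not support that.

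A reader might also infer that the plan prescribes observation-level degrees of freedom. It does not. It names software and no method, and an article may leave that to the analysis plan. The point is also minor: with about 1,558 df and no school-by-term variance the level held, and for school-by-term means a normal critical value in place of t on 27 df gave only 6.3-6.7%.

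Thirdly, the blind review may still change the model. That softens the point but does not answer it. The article names a concrete error structure and mentions no school-by-term effect, and an error structure chosen after looking at the data is weaker than one fixed beforehand.

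**Conclusion.** The point holds as a conditional one. The stated model lets nothing at school level vary over time, and the power calculation shares the gap. If school means vary from term to term beyond the common trend, the nominal 5% test runs at about 6% (CAC 0.99), 8-12% (0.95), 11-18% (0.90) or 17-28% (0.80). This rests on ICC 0.07, the stated attrition, roughly equal schools, and assumed within-student correlations of 0.3 to 0.7. Exactly zero school-by-term variance is the assumption that needs defending, and the article offers no defence. The fault lies in the missing variance component; the degrees of freedom are secondary. No design-based test is available at the 5% level, so the model's error term has to be right.

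**What to change.** Add a random school-by-term intercept to the primary model. Prespecify it now rather than at the blind review, and keep it even if its estimate is small or zero. Apply it to the secondary outcomes and the Māori subgroup as well. As a second safeguard, state Kenward-Roger or Satterthwaite degrees of freedom for the treatment effect (lmer with pbkrtest, or PROC MIXED with DDFM=KR) in place of the lme default. Restate power over a range of between-term correlations.

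The cost in work is one variance component and some wording, with no new data. The statistical cost is wider intervals and lower power if the variation exists. On the reading that reproduces the stated 83%, the standard error rises from 0.1706 to 0.186, 0.200 or 0.224, and power falls to about 77%, 71% or 61% at CAC 0.95, 0.90 or 0.80. With 27 df the critical value is about 2.05 instead of 1.96, a small further loss.

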#### Sample Size

Recruitment of 8 schools and data collection over 5 terms is judged feasible, with app implementation (the intervention) scheduled at 2 time points (terms 2 and 3, respectively, in the first year). We assumed roughly equal numbers of participants from each school. We use the method of Hussey and Hughes [59] to compute the power for different effect sizes under a model including the primary outcome (RSE), school-related random effect, and fixed effect associated with the term. The sample size computation was programmed in R version 3.x (R Foundation for Statistical Computing) by the study statistician in accordance with the analysis plan, including the specification that the intervention effect is assumed to be halved during the transition period. Other covariates may be included in the model, as decided during the blind review of the data.

Assuming an attrition of 35% (conservatively applied to all assessment time points postbaseline) and using a school-specific intraclass correlation of 0.07, evidenced in a bullying study in New Zealand schools [60], we estimate that recruiting 600 students is sufficient for detecting an effect size of 0.25 with 83% power and an effect size of 0.30 with 94% power. These correspond respectively and approximately to a change of 0.75 and 0.9 in the mean score of either component of the RSE score, based on the baseline data.

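### The printed power of 83% and 94% does not follow from the described model, which gives about 31% and 42% at 0.25 and 0.30 SD; the raw-score conversion implies an SD at the scale's maximum

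*Protocol article*

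**What the plan says.** The Sample Size section of the protocol article gives the method: "We use the method of Hussey and Hughes [59] to compute the power for different effect sizes". The model has the primary outcome, a "school-related random effect, and fixed effect associated with the term". The code follows the analysis plan, "including the specification that the intervention effect is assumed to be halved during the transition period". The remaining inputs are roughly equal school sizes, 35% attrition at every postbaseline assessment and a school intraclass correlation of 0.07. The result is that "recruiting 600 students is sufficient for detecting an effect size of 0.25 with 83% power and an effect size of 0.30 with 94% power".

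The next sentence equates these two effect sizes, approximately, with "a change of 0.75 and 0.9 in the mean score of either component of the RSE score, based on the baseline data".

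Three other places complete the inputs:
- Trial Design: "There are 5 assessments (web-based surveys) per school and 2 time steps over a 15-month trial period". Table 2 in that section shows 8 schools, with four in transition in term 2 and four in term 3.
- Analysis: "All tests will be performed at a 5% significance level against 2-sided alternatives".
- Table 3: each RSE component has two items scored "0=not at all confident 3=very confident", so each component runs from 0 to 6.

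**The concern.** This is the article's only quantitative justification for 600 students. It tells readers that the trial has more than 80% power for an effect of a quarter of a standard deviation. Two features call for a check. A two-step design over five terms with a half-weighted transition term leaves little contrast between treated and untreated schools within any one term. Separately, the conversion to raw points implies an SD that looks far too large for a 0-6 score. If the power figure is wrong, readers will misjudge how small an effect the trial was sized to detect on its primary outcome.

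**Working it through.** **Inputs**
- Schools I = 8, terms T = 5, two-sided alpha 0.05 (Trial Design, Table 2, Analysis).
- Treatment coding X = (0, 0.5, 1, 1, 1) for four schools and (0, 0, 0.5, 1, 1) for four (Table 2 with the halved transition effect).
- Students per school: 600/8 = 75 at baseline and 75 × 0.65 = 48.75 in terms 2 to 5.
- Total SD 1, so between-school variance t² = 0.07 and within-school variance 0.93 (Sample Size).

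**Described model.** Generalized least squares on school-by-term means, with a school random intercept and five term effects, gives SE = 0.1706 for the full effect. Power = Φ(d/SE − 1.96), ignoring the negligible opposite tail:

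| Full effect d (SD) | d/SE | Power | Printed |
|---|---|---|---|
| 0.25 | 1.465 | 31% | 83% |
| 0.30 | 1.758 | 42% | 94% |
| 0.50 | 2.931 | 83.4% | – |
| 0.60 | 3.517 | 94.0% | – |

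The printed pair needs an SE of 0.25/(1.960 + 0.954) = 0.0858, or 0.30/(1.960 + 1.555) = 0.0854. That is half of 0.1706.

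**Hand check by closed form**, taking 48.75 students in every cell. Let s² = 0.93/48.75 = 0.01908. The design sums are U = ΣX = 24, Q = ΣX² = 22, W = Σ(column sums)² = 168 and V = Σ(row sums)² = 74. For fractional coding:

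Var = I s²(s² + T t²) / [(I Q − W)s² + (U² + I T Q − T W − I V)t²]

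- Numerator: 8 × 0.01908 × (0.01908 + 0.35) = 0.05633.
- Denominator: 8 × 0.01908 + (576 + 880 − 840 − 592) × 0.07 = 0.1526 + 1.68 = 1.8326.
- Var = 0.03074, SE = 0.1753, power 30% at 0.25 and 40% at 0.30.

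This is slightly lower than the main result because baseline is also cut to 48.75.

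**Variants at 0.25 and 0.30**
- No attrition: 42% and 56%.
- Intraclass correlation from 0.01 to 0.15: 31-33% and 42-45%.
- One-sided test: 43% and 55%.
- Transition counted as fully treated, or fully control: 64% and 80%.

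None reaches the printed pair.

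**Routes that do give the printed pair**
1. The transition-term (half) effect was reported as the full effect. Full effects of 0.50 and 0.60 give 83.4% and 94.0%.
2. The usual closed form, which assumes X is 0 or 1 so that Q = U, was applied to X = 0.5. The denominator becomes 24 × 0.01908 + (576 + 960 − 840 − 592) × 0.07 = 0.4578 + 7.28 = 7.738. Then Var = 0.00728, SE = 0.0853 and power is 83.4% and 94.0%. This is not valid for fractional coding.
3. A within-participant correlation that the article does not state was used. A value of about 0.785 gives 83.0% and 93.8%; 0.75 gives 78% and 90%; 0.80 gives 85% and 95%.

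**Raw-score conversion.** 0.75/0.25 = 0.9/0.30 = 3.0. The SD of a score bounded by 0 and 6 is at most (6 − 0)/2 = 3, reached only with half the students at 0 and half at 6. Rounding does not help: 0.745/0.255 = 2.92. With doubled effect sizes, 0.75/0.50 = 0.9/0.60 = 1.5.

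**The case against.** The strongest reply is that the planned analysis is richer than the power model. The Analysis section specifies nested participant, year-group and school random effects, and students are surveyed repeatedly, so within-student correlation would add information. This stands in part. A reader might infer from the 31% that the trial as designed cannot see an effect of 0.25 SD, and the article does not support that. The gain depends on a correlation that is not given. Over an assumed range of 0.3 to 0.7, approximate power is 40-71% at 0.25 and 54-85% at 0.30, with year-group effects left out. That range still falls short of 83% and 94%, and the Sample Size section credits no such correlation.

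A reader might also infer that 0.25 and 0.30 are simply the halved transition effects. That route is the more economical, because it explains both the power and the SD of 3.0. It is not proven: the misapplied closed form gives the same rounded powers, and on that route 0.25 and 0.30 were the intended full effects.

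Nor can the SD be taken as 1.5. That figure is inferred from doubling the effect sizes, and no baseline SD is printed. If it proved right, 0.75 and 0.9 points would keep their 83% and 94% power under the described model, and only the standardized effect sizes would be wrong.

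Finally, what a null result excludes will depend on its confidence interval rather than on this sentence. That limits the consequence but does not make the printed figures correct.

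**Conclusion.** The power statement is wrong as written. Under the model the Sample Size section describes, power is about 31% at 0.25 SD and 42% at 0.30 SD, and 83% and 94% are reached at full post-transition effects of about 0.50 and 0.60 SD. The detectable effect is thus understated by a factor of two. The conversion to 0.75 and 0.9 points is separately not credible, because it needs the maximum possible SD of a 0-6 score.

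These figures rest on equal schools of 75, a total SD of 1, a normal-theory two-sided test, and only the school and term effects that the section names. They describe that power model and not the power of the planned mixed model, which may be higher by an amount the article does not allow one to calculate. The cause remains open: a half effect reported as the full effect, a closed form applied to fractional coding, or an unstated within-participant correlation of roughly 0.75-0.8.

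**What to change.** Re-run the power code and confirm the cause. In the Sample Size section:
- State that the effect size means the full post-transition effect in SD units.
- Subject to the re-run, restate power under the described model as about 31% and 42% at 0.25 and 0.30 SD, and 83% and 94% at 0.50 and 0.60 SD.
- Print the observed baseline SD of each RSE component and recompute the raw-point equivalents from it.
- If a participant-level correlation was used, or is to be credited because the planned analysis has a participant random effect, give its value, its source and the resulting power.

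The cost is one re-run and a few corrected sentences. Enrolment does not change, and the article already reports that schools were recruited and data collected, so this is a reporting correction. The stated sensitivity becomes less favourable unless a participant correlation can be justified.

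### The stated power does not follow from the stated model and inputs: effects of 0.25 and 0.30 SD have about 31% and 42% power, not 83% and 94%

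*Protocol article*

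**What the plan says.** Under Sample Size, the article uses the method of Hussey and Hughes with a school random effect and a fixed effect for term. It concludes that "recruiting 600 students is sufficient for detecting an effect size of 0.25 with 83% power and an effect size of 0.30 with 94% power". It says the calculation followed the analysis plan, "including the specification that the intervention effect is assumed to be halved during the transition period". The Analysis section fixes the reference for that halving: transition-term data are analysed "assuming an intervention effect half the size of that in the posttransition periods". The effect at full strength is therefore the post-transition effect. On the design, "Recruitment of 8 schools and data collection over 5 terms is judged feasible", with implementation "scheduled at 2 time points (terms 2 and 3, respectively, in the first year"). On cluster size, "We assumed roughly equal numbers of participants from each school". The Sample Size section then equates the two effect sizes with changes of about 0.75 and 0.9 points on either RSE component, citing baseline data. Table 3 scores each component from 0 to 6.

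**The concern.** The design carries little direct information. Under Table 2 the two groups of schools differ in exposure only in terms 2 and 3 of year 1, and by half a unit each time because of the halving. Power of 83% for a quarter of an SD looks too high for that contrast.

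This calculation is the article's only justification for 600 students. If it is wrong, a reader will think the trial more sensitive than its planning model supports. A non-significant primary result could then be taken as evidence that the app does not work, on the strength of a power figure that the stated inputs do not give. The same applies to any Māori subgroup result read against that figure.

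**Working it through.** **Inputs**
- Schools and terms: 8 and 5 (Sample Size).
- Layout: 4 schools per sequence (Table 2; Randomization, first sequence "year 1, term 2: 2 small schools, 1 large school with HRP, and 1 large school with no HRP").
- Students: 600/8 = 75 per school in term 1, then 75 × 0.65 = 48.75 in each later term.
- Variances: total 1, school 0.07, residual 0.93.
- Exposure: 0, 0.5, 1, 1, 1 for the first sequence and 0, 0, 0.5, 1, 1 for the second.
- Test: two-sided 5% (Analysis).
- Terms: taken as categorical, which the article does not state.

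**Standard error that the printed powers need**
- 0.25/(1.960 + 0.954) = 0.0858
- 0.30/(1.960 + 1.555) = 0.0854

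**Standard error from the stated inputs**

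With equal sequences and categorical terms, only the between-sequence difference informs the effect. The exposure difference by term is d = (0, 0.5, 0.5, 0, 0).
- Weight per term = 4n/(2 × 0.93), which is 161.3 in term 1 and 104.8 in terms 2 to 5. The weights sum to 580.6.
- The school variance of the difference is 2 × 0.07/4 = 0.035, with inverse 28.6.
- Information = Σwd² − (Σwd)²/(Σw + 28.6) = 52.4 − 104.8²/609.2 = 34.4.
- SE = 1/√34.4 = 0.1706. Generalised least squares (GLS) on school-by-term means gives the same value.

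Power = Φ(effect/SE − 1.96):

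| Full post-transition effect (SD) | Power |
|---|---|
| 0.25 | 31.1% |
| 0.30 | 42.0% |
| 0.50 | 83.4% |
| 0.60 | 94.0% |

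The SE is twice what the printed powers need.

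**Two routes that do return the printed figures**

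(a) Treat 0.25 and 0.30 as the halved transition-term effects, so that exposure is coded 0, 1, 2. The SE halves to 0.0853, giving 83.4% and 94.0%.

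(b) Keep 0, 0.5, 1 and use 48.75 students in every term, but apply the closed-form variance for 0/1 exposure, which relies on X² = X:

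Var = I·s²(s² + T·t²) / [(I·U − W)s² + (U² + I·T·U − T·W − I·V)t²]

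- I = 8, T = 5, s² = 0.93/48.75 = 0.01908, t² = 0.07.
- U = ΣX = 24. W (squared term totals) = 4 + 36 + 64 + 64 = 168. V (squared school totals) = 4 × 3.5² + 4 × 2.5² = 74.
- Numerator = 8 × 0.01908 × 0.36908 = 0.0563.
- Denominator = 24 × 0.01908 + 104 × 0.07 = 7.738. SE = 0.0853, giving 83.4% and 94.0%.
- The valid form replaces U by ΣX² = 22 where it stands for a sum of squares. The denominator is then 8 × 0.01908 + 24 × 0.07 = 1.833 and the SE is 0.1753, giving 29.7% and 40.2%.

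**Other readings of the inputs**

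| Variant | Power at 0.25 | Power at 0.30 |
|---|---|---|
| Linear term effect | 51% | 67% |
| No attrition | 42% | 56% |
| Intraclass correlation from 0 to 0.20 | 31–42% | 42–55% |
| Transition coded as full effect or as none | 64% | 80% |
| Full effect in transition and no attrition | 81% | 93% |

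The last row comes closest, but it drops two inputs that the article says were used.

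**Raw-score check**

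0.75/0.25 = 0.9/0.30 = 3.0. On a 0–6 score an SD of 3.0 is about the maximum possible, reached with half the students at 0 and half at 6.

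**The case against.** The strongest defence is that the planned analysis is not the power model. The Analysis section adds participant and year-group random effects, and the same students are invited to five surveys. A participant effect would raise power: if the within-school correlation between a student's repeated scores were 0.5, power would be about 51% and 67%; at 0.7, about 71% and 85%. This point stands, and the trial's actual power is therefore unknown. It does not rescue the printed figures. The power model has no participant effect, no within-student correlation is stated, and about 0.79 would be needed to reach 83% and 94%.

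A second defence is that 0.25 and 0.30 were meant as transition-term effects. The article does not say so, and its Analysis section anchors the halving to the post-transition effect. If that was the intention, the paragraph still needs correcting.

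A reader might go further and infer that the halving was applied in the wrong direction, with the raw scores as confirmation: at an SD of 1.5, 0.75 and 0.9 points would be 0.50 and 0.60 SD. The article does not support this. Route (b) gives the same powers without that slip, and an SD of 1.5 appears nowhere in it.

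**Conclusion.** The concern holds as a failure of the stated power to follow from the stated model and inputs. Power is about 31% at 0.25 and 42% at 0.30; 83% and 94% belong to full effects of 0.50 and 0.60 SD. The result assumes categorical terms, but a linear term also falls well short. The cause is undetermined. The raw-score sentence is doubtful on its own account.

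A reader might also infer that the trial would miss a true 0.25 SD effect about 7 times in 10, or that it needs about 2,400 students. Both belong to the simplified power model. They should not be carried over to the planned analysis, whose participant effect has no stated correlation.

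**What to change.** 1. Recompute power with a GLS (model-matrix) variance that is valid for fractional exposure. Recoding exposure as 0, 0.5, 1 in the existing program is not enough: if the 0/1 closed form is the cause, the same wrong figures will come back.
2. Define the effect size as the full post-transition effect and say how term is modelled.
3. Restate the paragraph as about 31% and 42% power at 0.25 and 0.30, or as 83% and 94% at 0.50 and 0.60.
4. Recheck the 0.75 and 0.9 point equivalents against the observed baseline SD, and print that SD.
5. If power is claimed for the planned model with a participant effect, state the within-student correlation assumed.
6. Do not interpret a null result against the printed 83%.

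The cost is one recalculation and one corrected paragraph. The Results section reports that the eight schools were recruited and data collected over five terms; conduct does not change and no extra students are needed. The stated sensitivity becomes less favourable.
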